## Reporting procedures for All serious Adverse Events

### Reporting procedures for Adverse Events

AEs will not be reported as part of this trial. AEs should be recorded in the medical records according to local practice.

### Reporting Procedures for Serious Adverse Events

Adverse events which meet the serious criteria (SAEs) and which are deemed related to the trial, except those identified as expected within section 9.1, occurring from point of randomisation and until follow-up completion (minimum of two years after trial treatment), must be reported to the Sponsor and the EVOCC trial management team immediately and within 24 hours of becoming aware of the event. The SAE will be reported using the current standard Sponsor SAE reporting form and according to the Sponsor SOP for reporting serious adverse events. For clarity, those listed in the above table as expected SAEs and SAEs that are deemed as **not** related to the trial do not need to be reported, only those events that fall outside of this list should be reported expediently as described. All exempt SAEs should be recorded in the patient medical notes as such.

**Please note:** **No serious adverse reactions (SARs) are anticipated as a unique consequence of participation in the EVOCC trial.**

The following information will be recorded for all SAEs:

- Description of the event
- Date of onset and end date
- Severity
- Assessment of relatedness to trial
- Action taken.

SAEs will be followed until resolution or the event is considered stable.

It will be left to the investigator’s clinical judgment whether or not an SAE is of sufficient severity to require the participant’s removal from the trial. The participant must undergo an end of trial assessment and be given appropriate care under medical supervision until symptoms cease or the condition becomes stable. The severity of events will be assessed on the following scale: 1 = mild, 2 = moderate, 3 = severe. The relationship of SAEs to the trial will be assessed by a medically qualified investigator.

Additional information will be provided if requested to the Sponsor and main Research Ethics Committee (REC). The Principal Investigator or another delegated physician (as agreed by the Sponsor) is responsible for the review and sign off of the SAE and the assessment of causality.

The Sponsor will perform an initial check of the information and ensure that the SAE line listing is reviewed by the Director of Research & Innovation. All SAE information must be recorded on an SAE form and sent to the Sponsor. Additional information received for a case (follow-up or corrections to the original case) needs to be detailed on a new SAE form and sent to the Sponsor.

Copies of all documentation and correspondence relating to SAEs will be stored in the TMF and ISF.

In addition to the expedited reporting above, the CI shall submit once a year throughout the trial or on request an Annual Report to the Ethics Committee which lists all SAEs that have occurred during the preceding 12 months.

The trends in these events will be independently reviewed in addition to the trial safety monitoring procedures. The decision regarding the frequency of review of individual and cumulative SAEs is to be based on the trial design, risk assessment and advice from the Sponsor / TSC / DMC and will include:

- Clinical review of a line listing of all life threatening or SAEs resulting in death within 1 week of their occurrence
- Clinical review of a line listing of all other SAEs on a monthly basis
- Cumulative review of all safety information by the DMC on an annual basis or more often if required

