# Outcome measures

## Primary outcome

Combined measure of death or major lower limb amputation, measured in days from randomisation until first event or until the end of the trial (minimum 2 years) where no event occurs.

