### Optional consent for linkage of NHS routine clinical datasets

EVOCC includes an optional consent to allow linkage to patient data available in NHS routine clinical datasets, such as the Hospital Episode Statistics (HES) and mortality data from the Office of National Statistics (ONS) through The Health and Social Care Information Centre and other central UK NHS bodies. This consent will also allow access to other new central UK NHS databases that may appear in the future so that relevant long-term outcomes and health resource usage data can be recorded to extend the follow-up of participants without needing to contact them further. This is important as it will link treatments that may become a clinical standard of care to long-term outcomes that are routinely collected in clinical data, but which will not be collected during the follow-up period of the trial.

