## Withdrawal of participation and consent criteria

Participants may withdraw their consent for the trial at any time if they choose not to continue, without prejudice for future care and they do not need to provide a reason why. However, if they are willing to provide a reason, it should be recorded on the relevant CRF. Participants will be asked to what extent they wish to withdraw their consent from the trial:

Prior to trial intervention, i.e., withdrawal from the trial intervention:

The participant would like to withdraw from their randomly allocated trial treatment i.e., they will not undergo the type of surgery as determined by randomisation, but will remain in trial follow-up and data will continue to be collected from them.

Post-trial intervention:

- Participant would like to withdraw from the attendance at clinic visits but gives permission for the trial related data to be collected from medical notes, NHS digital or contacted remotely (e.g., via telephone) to collect trial data
- Participant would like to withdraw from all trial assessments (both in person and remotely) but is happy for the study team to collect data from NHS databases in the future
- Participant would like to withdraw from the trial completely – no further data collection will be carried out

Withdrawal status will be documented on trial CRF and medical records. It is important to note that the data already collected prior to the point of withdrawal can still be analysed and included in the trial dataset.

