## Primary outcome analysis

The primary analysis of the primary outcome (amputation free survival) will compare the time to first event between randomised groups. The primary outcome will be defined as time to first event calculated by measuring in days the time from randomisation until first event or last known event-free observation during the follow-up period. Participants not experiencing a primary outcome event will have their time to event censored at last follow-up date. Participants withdrawing consent or that are lost to follow-up prior to reaching primary outcome will have their time to event at last contact date. The primary analysis will be undertaken on an intention-to-treat basis with all participants included post randomisation analysed in the group to which they were allocated. The primary outcome will be compared between randomised arms using restricted mean survival time carried out using a validated programme such as the Stata module ‘STRMST2’ or equivalent. A point estimate, 95% confidence interval and 2 sided p-value will be presented. Statistical significance will occur if the p-value is <0.05. The primary analysis will be adjusted for the minimisation factors used at randomisation. The individual components of the primary outcome will be reported separately as secondary outcomes

Secondary analyses of the primary outcome will explore a per-protocol population excluding major protocol deviators.

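### Section 9.2.2 lets an investigator remove a participant from the trial after a severe SAE without saying that follow-up for death and amputation continues, which conflicts with sections 8.7, 11.5 and 11.6.4

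*Protocol*

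**What the plan says.** - **Removal.** Section 9.2.2 leaves to the investigator's clinical judgement "whether or not an SAE is of sufficient severity to require the participant’s removal from the trial". The next sentence reads "The participant must undergo an end of trial assessment and be given appropriate care under medical supervision until symptoms cease", or until the condition is stable. Nothing is said about outcome data after removal, and the schedule of assessments (Table 2) lists no end-of-trial visit.
- **Withdrawal.** Section 8.7 is built on the participant's choice: "Participants will be asked to what extent they wish to withdraw their consent from the trial". A participant who declines the allocated procedure stays in follow-up. After the procedure there are three levels, and only complete withdrawal ends all data collection. No level covers removal by an investigator.
- **Primary outcome.** Section 4.1: "Combined measure of death or major lower limb amputation, measured in days from randomisation until first event or until the end of the trial".
- **Analysis.** Section 11.5: "The primary analysis will be undertaken on an intention-to-treat basis with all participants included post randomisation analysed in the group to which they were allocated". On censoring it says "Participants not experiencing a primary outcome event will have their time to event censored at last follow-up date", and "Participants withdrawing consent or that are lost to follow-up prior to reaching primary outcome will have their time to event at last contact date".
- **Missing data.** Section 11.6.4 states that time-to-event outcomes will not have missing data, and relies on routine data to limit losses.
- **Linkage.** Section 8.2.1: "EVOCC includes an optional consent to allow linkage to patient data available in NHS routine clinical datasets".

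**The concern.** Sections 7.1 and 7.2 compare revascularisation procedures. Once the procedure is done there is no continuing trial treatment to stop, so the natural effect of removal from the trial is that follow-up stops. The primary outcome is death or major amputation, and a patient with a severe SAE is plausibly at higher risk of both. Censoring such patients when they are removed breaks the independence between censoring and outcome on which the survival comparison rests. The decision would be taken by clinicians who know the allocation, because section 5 states that blinding is impossible.

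The intention-to-treat statement does not protect against this. It keeps removed participants in the allocated group but supplies no outcome after their last follow-up. Analysis cannot recover events that were never collected.

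**Working it through.** **1. Sections side by side.**

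| Question | 9.2.2 | 8.7 | 11.5 and 11.6.4 |
|---|---|---|---|
| Who ends participation? | Investigator, on SAE severity | Participant only | Not addressed |
| Is outcome follow-up kept? | Not stated; an end-of-trial assessment follows | Yes, wholly or in part, except on complete withdrawal | All randomised analysed; no missing time-to-event data expected |
| Where is a removed, event-free participant censored? | Not stated | Not covered | By the general rule, at last follow-up |

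Section 11.5 does not name investigator-removed participants. They fall under its general rule for participants without an event.

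**2. The design figures (section 11.1) reproduce.**
- Endovascular arm, event-free at 3 years: (1 - 0.2063)^3 = 0.500.
- Hazard ratio: ln(0.633)/ln(0.5) = 0.660.
- Sample size: 596/0.95 = 627.4, so 628.
- RMST to 3 years under exponential survival, with rate λ = -ln S(3)/3 and RMST = 12(1 - e^(-3λ))/λ months: 28.89 (open) - 25.97 (endovascular) = 2.92 months, matching the stated 3 months.

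**3. Illustration of the bias.** Each arm is a mixture of two exponential groups.
- A share p has an early severe SAE and event-free proportion b at 3 years. The rest have g = (S - p·b)/(1 - p), so the arm's true value S stays at 0.633 (open) or 0.50 (endovascular).
- A fraction f of the SAE group is removed and censored near time 0. The SAE share among those still observed is p' = p(1 - f)/(1 - p·f).
- The observed RMST is p'·RMST(b) + (1 - p')·RMST(g).

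The values of p, b and f are assumptions; the protocol gives none of them.

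Worked case, p = 10% open and 5% endovascular, b = 30%, f = 50% (314 × 0.10 × 0.5 ≈ 16 and 314 × 0.05 × 0.5 ≈ 8 removed):
- Open: g = (0.633 - 0.03)/0.90 = 0.670; p' = 0.05/0.95 = 0.0526.
- Endovascular: g = (0.50 - 0.015)/0.95 = 0.5105; p' = 0.025/0.975 = 0.0256.
- The difference in 3-year event-free proportion moves from 13.3 to 14.5 points, and the RMST difference from 2.85 to 3.13 months.

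| p open / endovascular | b | f | True RMST difference (months) | Observed | Bias |
|---|---|---|---|---|---|
| 10% / 5% | 30% | 50% | 2.85 | 3.13 | +0.29 |
| 15% / 5% | 30% | 50% | 2.79 | 3.29 | +0.50 |
| 15% / 5% | 15% | 50% | 2.59 | 3.35 | +0.75 |
| 10% / 10% | 30% | 50% | 2.87 | 3.02 | +0.15 |
| 10% / 5% | 30% | 10% | 2.85 | 2.90 | +0.05 |
| 2% / 1% | 30% | 50% | 2.91 | 2.96 | +0.05 |
| 5% / 10% | 30% | 50% | 2.92 | 2.86 | -0.06 |

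The result depends mainly on the share removed and on which arm has more removals.

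**4. A harsher stress test.** Suppose there is no true difference, and a share of the open arm's events in the first 6 months is censored one day before the event, with no removals in the other arm. In simulation (298 per arm, 3-year horizon, 2,000 replicates), a 25% share gives a spurious gain of about 0.7 month and two-sided rejection of about 11%; a 50% share gives about 1.4 months and 28%. With no removals, rejection is about 4%. The removals are one-sided by construction, so this shows that the mechanism can matter. It does not estimate what would happen.

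**The case against.** - **Section 9.2.2 does not say that data collection stops.** This is correct: removal from the trial is undefined. Only complete withdrawal by the participant ends data collection explicitly, and sections 8.4.2 and 8.5 allow follow-up from medical records. What stands is that the text permits the reading in which follow-up stops, and nothing excludes it.
- **Section 9.1 points the other way.** Serious complications such as bowel ischaemia and graft thrombosis are on the expected list, to be recorded on routine follow-up CRFs, which presumes that these patients stay in follow-up. This narrows the concern. It does not remove it, because the removal sentence refers to any SAE.
- **Removal could mean not receiving the allocated procedure.** SAEs count from randomisation, so one may occur before the procedure. Section 8.7 keeps a participant who then declines the procedure in follow-up, but says nothing about an investigator's decision.
- **Routine data would recover the events.** Linkage rests on optional consent, and section 9.2.2 does not direct its use after removal.
- **It is template wording.** That is plausible, since section 9.1 also defines reactions to an investigational medicinal product, which this trial does not have. It still instructs over 30 sites.

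A reader might infer that removals would be more frequent after open surgery and so favour the arm tested for superiority, given 3% against 1% early mortality. The documents do not support that as a conclusion. Those deaths are primary events, not removals, and the figures are unadjusted observational data. The SAE window runs to the end of follow-up, and the protocol also expects 43% re-intervention within 3 years and more late amputations and deaths after endovascular treatment (sections 1 and 2.2). Swapping the assumed SAE rates reverses the sign of the bias.

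**Conclusion.** The inconsistency is real. Section 9.2.2 allows removal from the trial by the investigator, is silent on later outcome collection, and does not fit sections 8.7, 11.5 and 11.6.4. If sites apply it as the end of follow-up, the primary outcome can be censored informatively by unblinded investigators.

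Direction and size cannot be determined from the protocol. In the mixture model the bias ranges from about -0.06 to +0.75 month on a 3-month target, or up to a quarter of it. The upper end needs half of a 15% SAE group in the open arm to be removed; with few removals the bias is about 0.05 month. The stress test goes higher only under one-sided assumptions that have no support in the text. This is a lower-severity point: a clarification to make because it is cheap and because uncollected outcomes may not be recoverable, not a defect that invalidates the design.

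**What to change.** Amend section 9.2.2, and cross-refer from section 8.7, to state that:

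- an SAE, or an investigator's decision following one, does not end outcome follow-up;
- death and major amputation, and the other outcomes where possible (including from medical records), are collected to the end of the trial unless the participant withdraws consent to data collection under section 8.7.

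The sentence requiring an end-of-trial assessment should be reconciled with this. Section 11.6.4 should acknowledge that censoring before the end of the trial can occur; any that follows an SAE can be reported by arm, with a sensitivity analysis. Clinical management after an SAE stays with the treating team and is not addressed here.

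The cost is a short protocol amendment and a note to sites. The sample size of 628 and the visit schedule do not change.

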### Reporting Urgent Safety Measures

The Sponsor, the Chief Investigator or the local Principal Investigator at a research site may take appropriate urgent safety measures in order to protect research participants against any immediate hazard to their health or safety.

If any urgent safety measures are taken the CI/Sponsor shall be notified immediately, and in any event no later than 3 days from the date the measures are taken, give written notice to the Sponsor and the relevant REC of: the measures taken; reason these measures taken; the circumstances giving rise to those measures and the plan for further actions.

# ROLES AND RESPONSIBILITIES OF TRIAL MANAGEMENT COMMITEES/GROUPS & INDIVIDUALS

## Trial Steering Committee (TSC)

The role of the TSC is to provide overall supervision for the trial on behalf of the Sponsor and Funder and to ensure that the trial is conducted to the rigorous standards set out in the Department of Health’s UK Policy Framework for Health and Social Care Research and the Guidelines for Good Clinical Practice. The remit of the TSC is to provide advice, focus on trial progress and adherence to study protocol, patient rights, safety and well-being as well as considering new information and its relevance to the research question. The TSC will also ensure that all ethical and regulatory approvals are obtained and agree proposals for substantial protocol amendments.

The TSC will be composed of an Independent Chair, and at least two Independent Clinicians or others with expertise relevant to the trial, along with a lay/PPIE representative. NIHR and Sponsor Representatives may be invited to attend TSC meetings as observers if required. The TSC will adopt a charter to define its terms of reference and operations. The TSC will have a majority independent representation, including the Chair, meet on an annual basis and send reports and make recommendations to the TMG/Sponsor/Funder. Members will be required to sign a ‘conflict of interests declaration form’.

## Data Monitoring Committee (DMC)

Independence is a key characteristic of a Data Monitoring Committee where the committee members are completely uninvolved in the running of the trial and thus cannot be unfairly influenced (either directly or indirectly) by individuals or institutions, involved in the trial. The role of the DMC is to monitor outcome data, safety data and other trial data and make recommendations to the TSC on whether there are any ethical or safety reasons why the trial should not continue. The safety, rights and well-being of the trial participants are of paramount importance, in addition to the validity of the trial data. The DMC will also consider data emerging from other related trials, provided by the Sponsor or Funder.

The DMC will consist of an Independent Chair, an Independent Clinician and an Independent Statistician. The DMC will adopt a charter, based on the principle of Damocles, to define its terms of reference and operation. The DMC will meet on annually as specified in the charter or more regularly in response to safety concerns or on recommendations by the committee themselves.

## Trial Management group

The TMG will be responsible for the day-to-day management of the trial to ensure the delivery through delegation of tasks to individuals or a group, for all aspects of the trial, including recruitment rate, budget management, safety reporting, protocol compliance and ensuring appropriate action is taken to safeguard trial participants and quality of the trial. The TMG members will meet regularly to ensure all practical details of the trial are progressing and working well.

# STATISTICS AND DATA ANALYSIS

## Sample size calculation

Calculations are based on our published meta-analysis, cohort study across multiple NHS hospitals treating patients with symptomatic PAD and aorto-iliac disease TASC II C and D with endovascular means, and contemporary NHS event rates in our HES analysis specifically for this trial (unpublished data). The perioperative mortality rate (at 30 days) for endovascular treatment is 1% in this unadjusted observational (non-randomised) data and 3% for surgery. Overall, 43% of patients undergoing endovascular treatment for these indications are expected to require re-intervention within 3 years. Based on a 20.63% event rate per year for endovascular treatment regarding amputation and/or death (national HES data), the proportion of patients for this arm free from death and amputation at 3 years is expected to be 50%. Further, based on HES data, the effect of both open surgery and endovascular treatment on the primary outcome is non-linear (more events in the first few months after the intervention), therefore the power calculation is based on an analysis with restricted mean survival time(8). Assuming a 2 year recruitment period and 3 year median follow-up, a sample size of 596 patients (accruing 256 events during follow-up) will provide 90% power (2 sided a=0.05) to detect an absolute risk reduction of 13.3% in terms of event-free survival (death or amputation) at 3 years (50% vs. 63.3% with a hazard ratio of 0.66) between arms (open surgery vs. endovascular treatment). This equates to an increase in restricted mean survival time (for death and/or amputation) of 3 months. Allowing for a conservative 5% loss of follow-up data (based on the completed NIHR HTA BASIL trials and given that the composite comprises of death or major amputation), the final sample size is 628 i.e. 314 participants per trial arm. Patients will be minimised based on age (above 65 years), sex and presence of tissue loss (yes/no) and stratified by site, which are the main factors predicting outcome after treatment for severe symptomatic PAD in multiple studies and similar NIHR HTA trials.

## Planned recruitment rate

The progression criteria for the internal pilot are based on 10 sites each recruiting on average 1 participant per month for 6 months. This equates to approximately 6% of eligible patients consenting to the trial. If the progression criteria from the internal pilot are met, we aim to recruit during the main phase from over 30 NHS sites over a further 2 years. Based on HES, a total of 2,200 eligible open surgery and 4,000 endovascular treatment procedures take place per year across approximately 30 of the vascular hospital networks that will take part in EVOCC. The targeted recruitment rate will remain at 6% throughout the main trial recruitment period.

